#### intracortical inhibition

- **Location & Assessment Team:** Data will be collected at the Ohio Musculoskeletal and Neurological Institute in Irvine Hall at Ohio University. Blinded members of The RELIEF Study Team (i.e., blinded students, staff, and the principal investigators) will be involved with the data collection and analysis.
- **Methods:** Data will be collected and analyzed as we have previously described [43]. In brief, electrical signals will be recorded bilaterally from the erector spinae (ES) muscles using bipolar surface electrodes located longitudinally over the muscle at the vertebral level of L2 and L4 on shaved and cleaned skin with a reference electrode located on the anterior superior iliac spine. The electromyogram (EMG) signals will be amplified (1000×), bandpass filtered (10–500 Hz), and sampled at 5,000 Hz. For the TMS measures, the center of a 110-mm double cone TMS coil will be positioned over the vertex. Single- and paired-pulse magnetic stimuli will be delivered using a Magstim 200^2 magnetic stimulator with the direction of current flowing from an anterior-to-posterior direction. During TMS, subjects were asked to sit with an upright posture while their hands rested in their lap. The TMS protocol will begin by delivering an initial single pulse at 50% of the maximum stimulator output to determine if this stimulus intensity is above or below motor threshold. Based on this finding the motor threshold will be determined by increasing or decreasing the stimulus intensity in 5% increments to determine the stimulation intensity where motor evoked potentials are consistently observed. Once the motor threshold is determined single pulses at intensity equal to 130% of motor threshold will be delivered to quantify motor evoked potential peak-to-peak amplitude. Next, intracortical facilitation will be quantified by delivering two pulses (conditioning and test pulse) with an interstimulus interval of 15-ms. The conditioning pulse intensity will be set to 70% of motor threshold and the test pulse intensity will be set to 130% of motor threshold. Short-interval intracortical inhibition will be assessed by delivering these pulses at the same intensity except with an interstimulus interval of 3-ms. A maximum of 6 trials for each outcome will be assessed in a blocked (a single pulse followed by the paired-pulse trials), with ~15-seconds separating each pulse sequence and ~60-seconds separating each block.

### 6.2.3 Blinding

In the RELIEF Study the principal investigators, statistician, and members of the data collection team will remain blinded to intervention assignment throughout the duration of the study. They will be given the identifying codes only at the end of the study when it is necessary to interpret the results of the study. To guard against un-blinding, only limited data categorized by intervention assignment will be released to the study investigators (e.g. adherence data), and these data will only be provided in aggregate. Secondly, the RELIEF Study Treatment Provider Team, who cannot be blind to the treatment assignment per se, will be blinded to the specific hypotheses of the study, and they will not be involved in any assessments or analyses. Lastly, the un-blinded study coordinator, who is responsible for scheduling testing and treatment sessions, will serve to receive the study patients and escort them to the various testing and

treatments sites to minimize the interaction between patients; however, the study coordinator will not participate in the assessments.

## **6.2.4 Follow-up Treatment Interventions and Assessments**

### Treatment Intervention 1 (visit 2)

- NPR (Assessed following treatment)
- Treatment Administration Form

The following physiological outcomes will be obtained immediately following the first treatment intervention based on the experimental group to which the participant was assigned to (i.e., muscular, spinal, cortical)

- Group 1 (Muscular Effects):
  - Skeletal muscle proton transverse relaxation time (T2) of the lumbar muscles.
- Group 2 (Spinal Effects)
  - Short-latency stretch reflex excitability.
  - Trunk muscle onset latencies in response to postural perturbations.
  - Lumbar motion during volitional movement tasks
  - Dynamic trunk stiffness
- Group 3 (Cortical Effects)
  - Motor evoked potential amplitude
  - Intracortical facilitation
  - Short-interval intracortical inhibition

### Treatment Intervention 2 (visit 3)

- NPR
- Expectancy/Credibility Questionnaire
- Prior & Concomitant Medication Form
- Change in Medication Use
- Treatment Administration Form

### Treatment Interventions 3-6 (visits 4-7)

- NPR
- Prior & Concomitant Medication Form
- Change in Medication Use
- Treatment Administration Form

### Assessments (visits 8 & 9)

The following clinical outcomes and evaluation data will be obtained from all study participants between days 23-25 of the study (post-treatment measures) and between days 57-61 of the study (follow-up measures):

- NPR

- RMDQ
- Prior & Concomitant Medication Form
- Change in Medication Use
- Treatment Administration

The following physiological outcomes will be obtained based the experimental group to which they are randomly assigned (i.e., muscular, spinal, cortical) 3-days +/-2-days (post-treatment measures) and 28-days +/-4-days (follow-up measures) following the final study intervention (visit 7):

- Group 1 (Muscular Effects):
  - Skeletal muscle proton transverse relaxation time (T2) of the lumbar muscles.
- Group 2 (Spinal Effects)
  - Short-latency stretch reflex excitability.
  - Trunk muscle onset latencies in response to postural perturbations.
  - Lumbar motion during volitional movement tasks
  - Dynamic trunk stiffness
- Group 3 (Cortical Effects)
  - Motor evoked potential amplitude
  - Intracortical facilitation
  - Short-interval intracortical inhibition

## 7. SAFETY ASSESSMENTS

Spinal manual therapies are some of the most common treatments for LBP, and the serious risks of manual therapies are infinitesimally small. However, there is a risk in performing manipulations on individuals with contraindications for this treatment (e.g., osteomyelitis, history of pathological fractures). However, these conditions are associated with other signs and symptoms that would be identified in a medical screening to rule out participants prior to enrollment in the study.

### 7.1 Specification of Safety Parameters

At visits 2-9 the study staff will use the Health Status Reassessment CRF to ask the study participants if they have had any change in general health since the last visit. If fever or unexplained weight loss is reported, suggesting systemic infection / disease may be causing their low back pain, the clinician will do a basic physical exam and specifically assess for the possibility they have other systemic illness. They will be advised to seek medical care and research participation may be delayed, temporarily discontinued, or permanently suspended at the discretion of the examining clinician and in consultation with the Medical Directors if needed.

Before each treatment the study staff will use the Contraindications for Intervention CRF to inquire about change in back related signs indicative of increased severity of symptoms. Specifically if they have any increases in 1) radiating pain (i.e., burning, numbness, tingling sensations into the legs), 2) have noticed any muscle weakness in the legs, and 3) have any episodes of incontinence of bowel or bladder. If the study participant reports yes on any of these items the clinician will do a basic physical exam and assess neurological function by checking

myotomes, dermatomes, and reflexes to determine whether the study participant now presents with hard neurological signs (e.g., loss of motor function, significant changes in reflexes), or symptoms of other systemic disease. If the participant does present with hard neurological signs or serious systemic disease, they will be encouraged to seek consultation with their personal physician, and they will be excluded from further participation from the study.

Before each experimental measurement lab testing session (Visits 2, 8, and 9) the study staff will use the Contraindications for Lab Testing CRF to inquire specifically about symptoms of health issues contraindicated for the allocated experimental measurement lab test. Migraine headache will be assessed using The ID Migraine™ self-administered screener. If a possible contraindication is identified the PIs are consulted to determine safety before the lab testing begins.

All negative changes in health status will be recorded as Adverse Events, logged, and reported per requirements of the Ohio University IRB and NIH-NCCIH. In the case of dismissal from the protocol for the above stated reasons, the Medical Safety Committee will meet to determine whether the AE was caused by the intervention (Definite, Probable, Possible, Unknown) and an adverse event report will be filed according to the specific requirements of the Ohio University IRB and NCCIH.

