#### **6.2.4 Follow-up Treatment Interventions and Assessments**

##### Treatment Intervention 1 (visit 2)

- NPR (Assessed following treatment)
- Treatment Administration Form

The following physiological outcomes will be obtained immediately following the first treatment intervention based on the experimental group to which the participant was assigned to (i.e., muscular, spinal, cortical)

- Group 1 (Muscular Effects):
  - oSkeletal muscle proton transverse relaxation time (T2) of the lumbar muscles.
- Group 2 (Spinal Effects)
  - oShort-latency stretch reflex excitability.
  - oTrunk muscle onset latencies in response to postural perturbations.

oLumbar motion during volitional movement tasks

oDynamic trunk stiffness

As the study is almost complete for the LBP participants, how will Dynamic Trunk Stiffness be measured in the LBP participants in Group 2? Was it previously assessed (e.g., as part of Trunk muscle onset latencies in response to postural perturbations) but not included explicitly within the protocol, or will the study only obtain it on LBP participants from this point forward, and if so, how many LBP participants will this include?

Regards,

[name]

[name], DC, PhD, DABCO  
Deputy Director, Division of Extramural Research  
National Center for Complementary and Integrative Health (NCCIH)  
National Institutes of Health (NIH)  
[name]  
[name]  
Office: [contact]; [contact]  
[contact]  
Web: [nccih.nih.gov](http://nccih.nih.gov)

[figure not shown]

---

**From:** [name] [<mailto:[contact]>]  
**Sent:** Wednesday, June 22, 2016 4:31 PM  
**To:** [name] (NIH/NCCIH) [E] <[[contact]](mailto:[contact])>  
**Cc:** [name] <[[contact]](mailto:[contact])>  
**Subject:** RELIEF Gender Supplemental

Dear [name],

Per our conversation last week, we have modified the DSP, e-crfs, ICF, and advertising flier to incorporate the changes associated with the funded gender supplemental. We took a mixed approach to update the DSP. That is we incorporated changes within the document where necessary, but also put a significant portion of the proposed new experiments in an appendix. The changes to the main document are highlighted in blue to ease the burden on the reviewers. Our intent is submit these changes to OU IRB as soon as we have approval from NCCIH. Please let me know if you require any additional information on this document.

Regards,

[name]

+++++

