Known and Potential Risks of the Treatment Interventions: Spinal manual therapies are some of the most common treatments for low back pain, and the risk of serious injury from the lumbar spinal manual therapy techniques is reported to be extremely small [49]. Gouveia recently conducted a systematic review to examine the adverse reactions associated with manual therapies. Their search identified 46 articles that included data concerning adverse events. With regards to lumbar (i.e., not cervical) manipulation, most of the adverse events reported were benign and transitory [49]. They did however report some cases of serious adverse events, such as disc herniation and progression to cauda equina syndrome [49]. However, others have estimated of the incidence of serious adverse events from published case reports and case series to be extremely rare (i.e., about 1 case event per 1 to 2 million treatments) [50]. A more common risk is soreness, which generally dissipates within hours to days.

Rationale regarding the supplemental research is included in the Appendix.

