Study Duration: The study duration for an individual participant with low back pain is ~ 8 weeks. Specifically, we expect that the typical amount of time between the event of enrollment ascertainment and randomization will be 3-5 days (maximum 7), and that randomization will occur when study participants begin a study intervention (visit 2). The study intervention will occur over a 3-week period followed by approximately 4-week follow-up. Thus, in total the study duration for an individual participant will be ~ 8 weeks. Specifically, in the first visit we will obtain informed consent and conduct a screening exam to determine if candidates meet the inclusion/exclusion criteria for a given experiment. If subjects meet the inclusion/exclusion criteria for an experiment they will be enrolled into the study and allocated to one of three experimental measurement groups (i.e., Muscular, Spinal, or Cortical). At the second visit, participants will then be randomized to an intervention arm (i.e., mobilization, manipulation, or laser), baseline assessments of both clinical and physiological outcome measures will be obtained, a treatment intervention will be performed, and clinical and physiological outcome measures will be repeated (i.e., follow-up assessment). Participants will then undergo an additional five treatments over the next three weeks (visits 3-7; total treatments: 6; treatment frequency: 2x/week). It should be noted that following treatment 1 we will assess expectancy and credibility expectations for the respective treatment intervention. Three days +/- 1-day after the final treatment, subjects will report back to the laboratory for a follow-up assessment of the clinical and physiological outcome measures (visit 8). Lastly, to determine the long-term effects of the interventions, subjects will report back to the laboratory approximately 4 weeks (28-days +/- 4-days) after their last treatment for the final follow-up assessment of the clinical and physiological outcome measures.

(visit 9). The study duration for a participant in the healthy control group is 3-hour including screening, baseline assessments, and lab testing. The anticipated duration for the RELIEF Study is 5-years. We anticipate the total enrollment time to take up to 4 years (48 months). The required monthly enrollment rate for study completion in the proposed time frame is 3.4 subjects/month.

Randomization, Stratification, and Blinding:

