## 4. SELECTION AND ENROLLMENT OF PARTICIPANTS

### 4.1 Inclusion Criteria

Participants must meet all of the following inclusion criteria to participate in this study:

- Between 18 to 45 years of age.
- Answer yes to the following questions
  - Have you had low back pain constantly or on most days for the last three months?
  - Has your back pain caused you to seek care or consultation from a health care provider?
- Average pain intensity, assessed using the Numerical Pain Rating (NPR) scale over the past week  $\geq 2$  on a 0-10 numerical pain scale
- Roland Morris Disability Questionnaire score  $\geq 4$
- Exhibit 3 of 4 of the following findings reported in the clinical prediction rules for spinal manipulation
  - No symptoms distal to the knee
  - FABQ work subscale score  $<19$
  - At least 1 hypo-mobile lumbar spinal segment
  - At least 1 hip  $> 35$  degrees internal rotation range of motion
- Exception: Participants in the healthy control group must report no low back pain (i.e., 0 rating on NPR, 0 score on Roland Morris Disability Questionnaire, and answer “No” to the following question: Have you had low back pain in the past 1-year that interrupted work/play or caused you to seek care from a healthcare provider?)

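### Minor safety improvement, not an error: the three directed neurological questions are asked after treatments 1 to 5 but not after treatment 6, and one existing form at Visit 8 would close the difference

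*Supplement*

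**What the plan says.** Section 7.1 sets up three inquiries.

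- **Open question, Visits 2 to 9.** The Health Status Reassessment form asks everyone about any change in health. For this question 7.1 names fever or unexplained weight loss as reasons for a physical examination.
- **Directed questions, treatment visits.** "Before each treatment the study staff will use the Contraindications for Intervention CRF to inquire about change in back related signs". The items are radiating pain, leg weakness and incontinence. A positive answer leads to a clinician's check of myotomes, dermatomes and reflexes. The form itself also sends it to the adverse event log.
- **Laboratory questions, Visits 2, 8 and 9.** The Contraindications for Lab Testing form depends on the laboratory group.

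In the case report forms shown (version 5.0), the directed form appears at Visits 2 to 7. It is not among the Visit 8 or Visit 9 forms or on their checklists. Section 3 places Visit 8 as follows: "Three days +/- 1-day after the final treatment". For the physiological outcomes, section 6.2.4 gives a wider window: "3-days +/-2-days (post-treatment measures) and 28-days +/-4-days (follow-up measures".

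**The concern.** Treatments 1 to 6 are given at Visits 2 to 7, so the form completed before treatments 2 to 6 also records what happened after treatments 1 to 5. Treatment 6 is the only one not followed by it. Whether a participant is then asked about leg weakness or incontinence depends on the laboratory group, which has nothing to do with exposure to manual therapy.

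Section 2.2 names disc herniation and cauda equina syndrome among the reported serious events of lumbar manipulation, and these three items ask about symptoms relevant to them. What is at stake is how fully milder new leg, bladder or bowel symptoms are picked up and referred after the last session. An open question may miss some of them.

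**Working it through.** **Inputs.** The enrolment table in section 3 gives, per arm, 14 Muscular, 20 Spinal and 20 Cortical participants, in three arms. Section 3 gives six treatments per participant. The items asked come from the Visit 7, 8 and 9 case report forms.

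**Plan's own figure.** Per arm 14 + 20 + 20 = 54, and 54 × 3 = 162. This matches the stated total.

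**Who is asked what after treatment 6.** The Visit 8 and Visit 9 laboratory forms have the same content.

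| Experiment | Items on the laboratory form | Of the three directed items |
|---|---|---|
| Muscular | magnetic field | none |
| Spinal | leg weakness, incontinence, new muscle, bone or joint injury | two |
| Cortical | magnetic field, migraine, benzodiazepines, concussion | none |

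The migraine and concussion items screen for fitness for magnetic stimulation, not for lumbar nerve symptoms.

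- None of the three items: 14 + 20 = 34 per arm. Manual therapy 2 × 34 = 68, sham 34, total 102. 102/162 = 63.0%.
- Two of three: 20 per arm, 60 in all (40 manual therapy, 20 sham).
- All three: 0 of 162. Radiating pain is not asked by name of anyone.

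**By manual-therapy session.** There are 2 × 54 = 108 participants and 108 × 6 = 648 sessions.

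- Followed by the full form: 108 × 5 = 540 (540/648 = 83.3%).
- Followed by two of three items: 40 (6.2%).
- Followed by none: 68 (10.5%).

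**Serious events.** Section 2.2 puts the rate at "about 1 case event per 1 to 2 million treatments". For the 68 sessions this gives 68/2,000,000 = 0.000034 to 68/1,000,000 = 0.000068 expected events.

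**What remains in place at Visits 8 and 9.**

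- All 162 get the open health-change question.
- All get both medication forms. One covers medication, heat or ice used for back pain (since the last visit at Visit 8, past 7 days at Visit 9). The other covers changes in medication unrelated to back pain in the past 7 days, and sends a negative health change to the adverse event log.
- The clinician's reassessment form is completed when the Health Status Reassessment indicates it, and it has a neurological line.

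**Routing compared.** The Visit 7 directed form sends a positive answer to the clinician's examination and the log. The Visit 8 and 9 open form says to record, alert the coordinator and log. The laboratory form says to refer to the principal investigators and log. The examination is available, but no Visit 8 or 9 form tells staff to send a leg symptom to it.

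**The case against.** The form is titled and placed as a check before treatment, and after treatment 6 there is nothing left to withhold. Nothing in the protocol calls it the check on the preceding treatment. The team also considered the late visits: the revision history of the forms records that the Health Status Reassessment was expanded to capture adverse events better and was added to Visits 8 and 9. Sections 7.1, 7.2 and 7.5 add that negative health changes are logged, side effects are monitored at every visit and events are followed to resolution. Choosing open over directed questions is a choice between acceptable methods. All of this stands, and it is why the point is an improvement and not a fault. What survives is that the plan itself adds directed items to the same open question at Visits 2 to 7, and their answers feed the adverse event log.

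A reader might infer more than the documents support:

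- **That safety follow-up stops after treatment 6.** It does not, as the open question and the medication forms show.
- **That the arms are compared unfairly.** Treatment is randomised within each experiment, and 34 of 54 in every arm get none of the items.
- **That serious events would be missed.** The expected number is below 0.0001.
- **That leg symptoms cannot reach an examination.** The reassessment form allows it; only an explicit instruction is lacking.
- **That Visit 9 must be included too.** Treatments 1 to 5 each have one directed check, at the next visit. Visit 8 alone gives treatment 6 the same.

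The unseen documents also matter. The correspondence on version 6.0 says: "we have modified the DSP, e-crfs, ICF, and advertising flier". Those electronic forms and the Data and Safety Monitoring Plan cited in section 7.6 are not shown.

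**Conclusion.** The difference is real but minor. After treatment 6, 102 of 162 participants (68 manual therapy, 34 sham) get none of the three directed items and 60 get two; none is asked about radiating pain by name. The harm rationale applies to the 68. No endpoint, between-arm comparison or serious-event risk is materially affected. The benefit is modestly better detection and referral of new leg, bladder or bowel symptoms. It cannot be sized, because the documents give neither the frequency of such symptoms nor the miss rate of the open question.

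The counts assume full planned enrolment and that the version 5.0 forms reflect practice.

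**What to change.** Extend the timing in section 7.1 from each treatment to each treatment and Visit 8. Add the existing three-item form to the Visit 8 checklist for all arms and all three experiments.

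- **Wording.** Ask about symptoms that are new or increased since the last visit. Eligibility requires a participant to "Exhibit 3 of 4 of the following findings reported in the clinical prediction rules for spinal manipulation", so some may enter with symptoms below the knee.
- **Blinding.** Use it in every arm, since a form given only to the manual-therapy arms would reveal allocation to assessors.
- **Order.** Ask it after the pain rating, disability and PROMIS questionnaires, so that it cannot influence the clinical outcomes.
- **Routing.** Send a positive answer to the adverse event log and the existing reassessment examination. The principal investigators decide whether laboratory testing is safe. Do any non-urgent reflex or myotome examination after that testing, so that it does not disturb the stretch-reflex outcome.
- **Examiner.** Section 6.2.3 says of the treatment providers that "they will not be involved in any assessments or analyses". This is a safety examination and not an outcome assessment, but where possible it should not be done by the participant's own provider.
- **Outcomes.** A positive answer should not stop collection of the clinical outcomes, in line with section 8.

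Repeating the form at Visit 9 is optional extra surveillance.

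**Cost.** A wording amendment and at most 162 one-page forms (108 manual therapy, 54 sham) at an existing visit, with an occasional examination by an existing clinician. If 1% to 5% of forms were positive (an assumed range; the documents give no rate), that is 162 × 0.01 = 1.6 to 162 × 0.05 = 8.1 examinations over the trial. If the monitoring plan or the version 6.0 forms already contain the items, a cross-reference in 7.1 is all that is needed.
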